**Biochemical tests**
Leukocyte, lymphocyte and platelet counts, ferritin, lactate dehydrogenase, troponin, creatine kinase, aspartate aminotransferase, alanine aminotransferase, and creatinine
**Hormone evaluation**
Prolactin and cortisol
**Thorax computed tomography**
Ground-glass opacity (<25%, 25-50%, >50%)Consolidation
**Serum immune biomarkers**
Chemokines: CXCL8, CCL11, CCL3, CCL4, CCL2, CCL5, and CXCL10; inflammatory cytokines: IL-1β, IL-6, TNF-α, IL-12p70, IFN-gamma, IL-17A, and IL-15; regulatory cytokines: IL-1Ra, IL-4, IL-5, IL-9, IL-10, and IL-13; and cell growth factors: IL-2, IL-7, FGF-basic, PDGF, VEGF, G-CSF, and GM-CSF
**Gene expression assays**
IFN-γ, IL-12, IL-17a, TNF-α, IL-6, IL-4, IL-5, IL-10, IL-1b, RANTES, MCP-1, MIP, MIG, IP-10, and IL-8
**Leukocyte phenotyping**
CD3, CD4, CD8, HLA-DR, CD25, CD19, CD5, CD27, CD38, PD-1, CD28, CD14, CD16, and CD56
**Leukocyte functionality**
IL-1β, IL-6, TNF-α, IFN-α, IL-5-PE, and IL-10
**Metabolomic analysis**
Metabolic profile/pathways

### Timeline

The TARGET protocol comprises two arms, referred to as the timeline (T)-branch and the days of hospitalization (D)-branch. For the purposes of this study, the T-branch refers to patients with mild/moderate forms that did not require hospitalization. The D-branch refers to patients with severe/critical forms who required hospital admission. Patients on the T-branch will be analyzed on days 0, 9, and 18 (T0, T9, and T18), while patients on the D-branch will be analyzed on days 0, 3, 9, and 18 (D0, D3, D9, and D18; Figure 1).

### Biological Samples

The TARGET protocol encompasses the collection of blood samples in four different types of containers. For these purposes, whole peripheral blood samples will be collected in vacuum tubes without an anticoagulant (10 mL) to obtain serum samples for metabolomic and biochemical analysis, in sodium citrate (5 mL) for coagulation assays, and in heparin (10 mL) to obtain plasma samples and to isolate polymorphonuclear and peripheral blood mononuclear cells (PBMC). Samples will be collected at distinct time points as follows: day 0, at inclusion by confirmation of COVID-19; day 3, within 2-4 days after inclusion; day 9, within 7-10 days after inclusion; and day 18, within 15-20 days after inclusion (Figure 2).

**Figure 2 figure2:**
[figure not shown]
Timeline showing the times of blood tests and the analysis performed. The upper line represents the duration of symptoms, a parameter used in the group of patients enrolled for prospective follow-up, composed primarily of patients who will evolve with mild conditions. The lower line represents the blood test dates in the hospitalized group: patients who have already entered the study with moderate to severe conditions, usually from the fifth day of symptom onset.

### Preanalytical Sample Handling and Preprocessing

The whole blood samples will be processed to obtain serum or plasma samples and PBMC batches. Tubes will be centrifuged at 1900 g for 10 minutes at 22 °C to obtain serum or heparinized plasma and processed immediately within-facility for routine PBMC isolation and cryopreservation [17].

### Clinical Biochemistry and Hematologic Analysis

Plasma samples obtained in ethylenediamine tetraacetic acid will be immediately analyzed at local clinical laboratory facilities. Biochemical analysis will be performed with a Rocas Cobas E411 system using compatible reagents to assess the levels of ferritin, troponin T, creatine kinase, creatinine, aspartate aminotransferase, and alanine aminotransferase. All procedures will be performed according to the manufacturer’s recommendations. Cortisol and prolactin in serum samples will be quantified at the Sabin Medicina Diagnóstica (Brasília, Brazil) using the chemiluminescent method (Siemens, Advia Centaur). Hematological analyses will be performed using whole blood obtained in sodium citrate tubes in an ABBOTT Cell Dyn 3700 analyzer or equivalent with samples from days 0, 9, and 18.

The coagulation profile will be assessed at the DASA Laboratory (Brasília, Brazil) by thromboelastometry tests carried out within a 3-hour interval after blood collection [13,25] as follows: extrinsic system assay (EXTEM), intrinsic system assay (INTEM), fibrinogen assay (FIBTEM), and nonactivated coagulation assay (NATEM; ROTEM, Werfen, Barcelona, Spain; Figure 3).

**Figure 3 figure3:**
[figure not shown]
Thromboelastometry method for clot evaluation. A pin that spins around its own axis is put in contact with a citrated blood sample inside a cuvette. After recalcification and addition of a specific activator (depending upon the test), the clotting starts, and as it gets firmer, the spinning capacity of the axis is reduced, which is transformed by the system in a graphic representation of the clot, with increasing amplitude. As the fibrinolysis starts, the clot becomes less firm, which is represented as decreasing amplitude on the monitor. The extrinsic system assay (EXTEM)'s activator is thromboplastin and evaluates the extrinsic activation of coagulation. The intrinsic system assay's activator is elagic acid and evaluates the intrinsic activation of coagulation. The fibrinogen assay's activator is the same as EXTEM plus cytochalasin D, which inhibits platelet activity. This depicts only the participation of fibrinogen in the clot. The nonactivated coagulation assay is recalcified blood and is a nonactivated evaluation of coagulation. Circulating tissue factors, such as those expressed on monocytes in inflammatory states, will start the coagulation process. CT is the time frame from activation until an amplitude of 2 mm and represents thrombin formation. CFT represents the dynamic formation of thrombin and is the time frame between 2 mm and 20 mm of clot amplitude. A10 represents the clot amplitude 10 minutes after initiation and is directly related to MCF, enabling the clinic to make important decisions. MCF is the maximum amplitude of the clot and represents its main constituents, namely, fibrinogen and platelets. ML represents the percentage of clot reduction after initiation of fibrinolysis. Therefore, 60 minutes after initiation, thromboelastometry depicts important information about every phase of the coagulation process. A10: amplitude in 10 minutes; CFT: coagulation formation time; CT: coagulation time; MCF: maximum clot firmness; ML: maximum lysis.

### Assessment of Molecular and Cellular Immunological Biomarkers

Serum biomarkers will be assessed using the Luminex Bio-Plex Pro platform set for 27 human immune mediators (Bio-Rad Laboratories, California) for the simultaneous assessment of the following analytes: chemokines (CXCL8, CCL11, CCL3, CCL4, CCL2, CCL5, and CXCL10), proinflammatory cytokines (IL-1β, IL-6, TNF-α, IL-12p70, IFN-γ, IL-17A, and IL-15) and regulatory cytokines (IL-1Ra, IL-4, IL- 5, IL-9, IL-10, and IL-13), and cell growth factors (IL-2, IL-7, FGF-basic, PDGF, VEG, G-CSF, and GM-CSF). All procedures will follow the manufacturer’s recommendations, with levels obtained at days 0, 3, and 9.

The expression levels of immune mediators will be assessed by TaqMan quantitative RT-PCR (qRT-PCR) assays (Applied Biosystems, Foster City, CA) for each transcript, with retro-transcription set up with 1 ng/μL of RNA from PBMCs and from neutrophils. The reactions will be carried out on a QuantiStudio 3 Thermal Cycler (Applied Biosystems, CA) in standard mode [26]. Alternatively, qRT-PCR experiments for selected genes will be based on the SYBR Green (family of dyes for molecular biology) detection methodology using the SYBR Green PCR Master Mix and universal cycling conditions on the ABI Prism 7000 Sequence Detection System. Expression levels will be assessed on days 3 and 9.

Immunophenotypic/functional profiles of circulating leukocytes will be assessed upon short-term culture in vitro. The cell suspension will be stained with distinct panels of monoclonal antibodies comprising CD3, CD4, CD8, HLA-DR, CD25, CD19, CD5, CD27, CD38, PD-1, CD28, CD14, CD16, and CD56 for cell surface analysis, and IL-1β, IL-6, TNF-α, IFN-α, IL-5-PE, and IL-10 for evaluation of intracytoplasmic functional status. Cells will be run on a FORTESSA flow cytometer (BD Bioscience, CA). An average of 100,000 cells will be analyzed per sample. The phenotypic/functional parameters will be assessed using FlowJo software (BD, New Jersey). Leukocyte phenotyping will be obtained at days 0, 3, and 9.

The immunoglobulin profile will be assessed by multiplexed PCR using cryopreserved PBMCs [19,27]. Sequencing libraries will be produced and sequenced using the Illumina MiSeq 2x300 bp platform. For each sample, 1 million reads corresponding to IgG and IgA will be produced. The reads will be processed using pRESTO [28], Ig heavy chain genes will be annotated using the MIXCR platform [29], and clonotypes will be determined as described in [30]. The immunoglobulin profile will be assessed in samples obtained on day 3.

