Hence, COVID-19 resembles a hyperimmune syndrome defined by potentially lethal hypercytokinemia due to overproduction of a set of proinflammatory mediators, including interleukins (IL-1β, IL-2, IL7), granulocyte colony stimulating factor, interferon-gamma (IFN-γ), monocyte chemoattractant protein-1 (MCP-1), and tumor necrosis factor-alpha (TNF-α), which culminates in multi-organ failure [8,9]. In addition, the Th17-type response plays an important role in severe cases due to an additional proinflammatory overflow resulting from supraphysiological IL-1β, IL-6, and TNF-α levels that contribute to edema formation [10]. The role of cortisol and prolactin in the modulation of the immune system has long been described [11,12], but their participation (if any) in the COVID-19–related “cytokine storm” remains unknown. Moreover, given the intimate interplay of inflammation with blood clotting, severe patients usually show a hypercoagulable profile that leads to an increased frequency of pulmonary thromboembolism, deep vein thrombosis, and even heart and brain ischemia events [13,14].

In this context, it is also no surprise that the first treatment that reduced COVID-19 mortality, in a large randomized controlled trial (RECOVERY [Randomised Evaluation of COVID-19 Therapy]) [12,15], was dexamethasone, a corticosteroid [12]. However, it also showed that the effect seems to depend on the clinical stage of the disease, highlighting the need for further investigations into the course of the inflammatory response. Other anti-inflammatory treatments such as tocilizumab, an IL-6 receptor-blocking humanized antibody used to treat rheumatoid arthritis, were used (out of compassion) in patients with severe COVID-19 in China and Italy [16-18], with some clinical improvement. Similarly, another drug under evaluation is baricitinib, a JAK2 inhibitor approved for myeloproliferative neoplasms and rheumatoid arthritis that reduces Th17-type cytokine secretion by blocking AP2-associated protein kinase 1 [19]. However, the clinical efficacy of baricitinib against COVID-19 has yet to be proven. These studies support the assumption that a cytokine “storm” not only plays a role in COVID-19 pathophysiology but also has predictive prognostic value to monitor the evolution of mild and severe cases.

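### CCL5, PDGF and VEGF are measured in clotted serum, so their mild-severe contrast may partly reflect platelet number or clotting in the tube instead of circulating levels

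*Protocol article*

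**What the plan says.** The section Assessment of Molecular and Cellular Immunological Biomarkers sets the matrix: "Serum biomarkers will be assessed using the Luminex Bio-Plex Pro platform set for 27 human immune mediators", with levels on days 0, 3 and 9. The analytes include "chemokines (CXCL8, CCL11, CCL3, CCL4, CCL2, CCL5, and CXCL10") and "cell growth factors (IL-2, IL-7, FGF-basic, PDGF, VEG, G-CSF, and GM-CSF"), where VEG is evidently VEGF. Textbox 1, under its serum immune biomarkers entry, has "cell growth factors: IL-2, IL-7, FGF-basic, PDGF, VEGF, G-CSF, and GM-CSF".

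Biological Samples describes the tubes: "whole peripheral blood samples will be collected in vacuum tubes without an anticoagulant (10 mL) to obtain serum samples for metabolomic and biochemical analysis", and separately "in heparin (10 mL) to obtain plasma samples and to isolate polymorphonuclear and peripheral blood mononuclear cells (PBMC"). No soluble-mediator assay is assigned to the heparin plasma. Preanalytical Sample Handling and Preprocessing gives one spin (1900 g, 10 minutes, 22 °C) and no clotting time.

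On clotting, the Introduction says that "severe patients usually show a hypercoagulable profile". Textbox 1 lists enoxaparin among recorded COVID-19 treatments, while Recruitment applies the anticoagulant exclusion only to the coagulation tests.

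Statistical Analysis compares soluble biomarkers between severity groups by t test or ANOVA, or by Mann-Whitney or Kruskal-Wallis. It then derives ROC cutoffs from single or combined biomarker scores. Textbox 1 lists platelet counts among the biochemical tests.

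**The concern.** A serum value of a platelet-stored mediator combines what circulated in the patient with what the platelets released while the blood clotted in the tube. If platelet number or the extent of clotting differs between the branches, the serum contrast can move although circulating levels are the same. Neither blinding of laboratory staff nor a larger sample removes this, because it arises in the specimen.

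What is at stake is interpretation. A contrast in CCL5, PDGF or VEGF could be reported as an immune or growth-factor signature of severity, and could enter the combined ROC score as such, when part of it is a platelet effect.

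**Working it through.** The article states no figure on this point, so there is none to reproduce. The check has two parts.

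**1. Does the article fix the premises?**

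- *Matrix.* The Introduction, Textbox 1 and the biomarker section all say serum. Biological Samples assigns the serum tube to metabolomic and biochemical work without naming the panel, but nothing in the article points to plasma for it.
- *Clotting in the tube.* Serum tubes contain no anticoagulant, so release on clotting applies.
- *Possible differences between branches.* The Introduction expects hypercoagulability in severe patients. Anticoagulant users stay in the serum panel because their exclusion covers the coagulation tests only. Neither statement gives a platelet count by branch or a difference in release within a plain tube.
- *Analysis.* The tests named for soluble biomarkers are unadjusted.
- *Availability of counts.* The hematology text in Clinical Biochemistry and Hematologic Analysis uses samples from days 0, 9 and 18. Table 1 ticks biochemical tests, under which Textbox 1 places platelet counts, on day 3 as well. Counts are therefore clear for days 0 and 9 and uncertain for day 3. Under Timeline, day 3 is a D-branch visit only, so it bears on the course within severe patients and not on a same-day mild-severe contrast.

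**2. How large could the effect be?**

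Let *f* be the share of the serum level released by platelets in the tube and *r* the relative shortfall in platelet count in one branch. Circulating levels are taken as equal. The serum ratio between branches is then

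ratio = (1 − f) + f(1 − r) = 1 − f·r.

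On the log scale, SD = √ln(1 + CV²): √ln(1.16) = 0.385 for CV 40% and √ln(1.36) = 0.555 for CV 60%. With 100 per group (the planned 200 split 1:1), SE = SD·√(2/100) = 0.0545 and 0.0784. The chance of a significant result in the direction of the artefact is Φ(|ln ratio|/SE − 1.96). Without any artefact it would be 2.5%.

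| f (assumed) | r (assumed) | Ratio | Chance, CV 60% | Chance, CV 40% |
|---|---|---|---|---|
| 0.30 | 0.10 | 1 − 0.03 = 0.97 | 6% | 8% |
| 0.60 | 0.20 | 1 − 0.12 = 0.88 | 37% | 65% |
| 0.90 | 0.30 | 1 − 0.27 = 0.73 | 98% | 100% |

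Worked row: |ln 0.88| = 0.128. At CV 40%, 0.128/0.0545 = 2.35 and Φ(0.39) = 0.65. At CV 60%, 0.128/0.0784 = 1.63 and Φ(−0.33) = 0.37.

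The values of f, r and CV are all assumptions. Over this range the artefact runs from negligible to dominant. If platelets were higher in the severe branch, the sign would reverse.

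**The case against.** The strongest reply is that the article shows no difference between branches in the quantity that matters. It gives no platelet count by branch, and hypercoagulability in the patient is not the same as greater release in a plain tube. This stands: the differential effect is plausible but not demonstrated. Serum is also a legitimate matrix choice and not a handling error, and the article labels the values as serum throughout. A reproducible serum marker can classify severity whatever its cellular source. That also stands, and it confines the concern to calling such a marker an immune signal.

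A further reply is that covariates and score composition may be settled in an analysis plan that is not shown. That is fair, and a missing covariate is not the point here. The point is the matrix, which the article fixes; a later covariate would handle its consequence without changing it.

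A reader might infer that these serum values are mainly platelet content, that a severity signature will follow, or that the bias is of a definite size. An assumed share of 50-90% with an assumed 30% platelet difference would give 0.5 × 0.30 = 15% to 0.9 × 0.30 = 27%. The article supports none of these readings, because it gives neither input and platelet number and clotting activation could act in opposite directions.

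**Conclusion.** The concern holds as a limit on interpretation for three of the 27 analytes. Their mild-severe contrast may partly reflect platelet number or clotting in the tube. This rests on the serum matrix fixed in the article and on the general laboratory fact that platelets release these mediators when blood clots. It does not extend to the whole panel, and TNF-α, on which the sample size rests, is not among the analytes named. Size and direction are unknown, and the table above is illustrative only. This is a minor, low-cost improvement and not a flaw that undermines the study.

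**What to change.** In Statistical Analysis, for CCL5, PDGF and VEGF:

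1. Report the severity contrast both unadjusted and adjusted for the same-visit platelet count, on days 0 and 9. Apply the same adjustment to day-3 values once Table 1 and the hematology text are reconciled on whether counts exist then.
2. State that the serum values include platelet release.
3. Report the combined ROC score with and without these three analytes, and call them immune-mediator signals only if the association survives adjustment.

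The cost is one covariate already collected and a second version of the score; no new blood draw is needed. The downside is that platelet count may be a consequence of severity, so adjustment can remove real signal. That is why both results should be shown.

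Measuring the three analytes in stored heparin plasma is optional. It depends on spare volume, which the article does not state, and on residual platelets after the single spin. Plasma values would also be lower, with more results near the detection limit, and would not be comparable with published serum values.

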### Neutrophil Evaluation Experimental Design and Groups

Neutrophils will be obtained from healthy donors and from patients at two different times, T9/T18 and D9/D18. Neutrophils isolated from each donor will be divided into two aliquots and incubated in buffer (control group) or phorbol 12-myristate 13-acetate (PMA; activated group). Cells from each group will be submitted to the functional and molecular analyses described in the following sections.

### Neutrophil Isolation and In Vitro Activation

Cell isolation will be performed from peripheral venous blood by centrifugation in Percoll gradients, as previously described [27]. The remaining erythrocytes will be removed by hypotonic lysis. Samples containing >95% neutrophils and >98% viable neutrophils will be prepared in 50% autologous plasma and divided into aliquots for control or activation in PMA [28].

### Evaluation of Reactive Oxygen Species Production and Phagocytosis

The isolated neutrophils, after incubation in each condition, will be tested for reactive oxygen species production as described by Tahir et al [29].

### Evaluation of Neutrophil Extracellular Traps Production

At the final 20 minutes of incubation in each condition, an aliquot of neutrophils will be removed and incubated with SYTOX green (high-affinity nucleic acid stain; 10 µmol/L) and 4′,6-diamidino-2-phenylindole (blue-fluorescent DNA stain; 1 µg/mL). Fluorescence readings will be performed both by fluorescence microscopy and on a spectrophotometer [30].

### Real-time Migration Assay

Neutrophils from each condition will be applied to the upper chamber of a xCELLigence Real-Time Cell Analysis instrument and dynamically measured regarding the migration toward the chemoattractant N-Formylmethionyl-leucyl-phenylalanine (potent polymorphonuclear leukocyte chemotactic factor) [31].

### Neutrophil Proteomics

Neutrophils obtained in all experimental conditions will be subjected to cell lysis by ultrasound cavitation and then trypsin digested. Eluted peptides will be subjected to capillary chromatography in a two-column online vented system. The fractions will be eluted directly into the ionization chamber of an Orbitrap Elite mass spectrometer to be analyzed in data-dependent acquisition mode. The 20 most intense ions will be selected for high-energy collision dissociation fragmentation, and the fragments will be analyzed in the ion-trap detector. Mass spectra will be analyzed for protein quantification and identification using the Progenesis and Peaks software packages, as well as in-house developed R scripts for statistical analysis [32].

### Metabolomic Profiling

We will aim to analyze each serum sample collected from mild (T-branch group) and severe (D-branch group) case patients and healthy volunteers at each time point in the same manner (Figures 1 and 2). Untargeted metabolomics will be performed using a Bruker UPLC-PDA-QqTOF (ultra-performance liquid chromatography photodiode array quadrupole-quadrupole-time-of-flight) compact (UPLC-MS/MS). The obtained data will be used to build molecular networking using the Global Natural Products Social Molecular Networking platform, which gives a better overview of the metabolic profile and group compound classes in clusters. For statistical validation of the metabolite differences between the groups, the data will be processed in MZmine and analyzed by means of chemometric tools, as provided by the MetaboAnalyst platform. Based on this broad chemical outline, specific metabolites will be quantitatively analyzed using targeted metabolomics using a CLAE Quadrupole/Quadrupole. This approach will be used to validate and quantify specific components of interest, such as metabolites involved in the glycolytic and hexosamine pathways, and tricarboxylic acid cycle, among other possible biomarkers.

### Sample Size Calculation

The sample size calculation was based on the assumption that 20% of patients who are critically ill have elevated TNF-α levels compared to 5% of patients who are noncritically ill [8]. TNF levels will be normalized according to the study population. Based on a bilateral 95% significance level, a power of 80%, and a case-control ratio of 1, a sample size of 200 patients can be predicted.

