## Methods

### Study Design and Population

TARGET is registered in the Brazilian Clinical Trials database with registry code RBR-62zdkk and constitutes a multicenter, prospective cohort study of consecutive COVID-19 cases, consisting of participants recruited from secondary and tertiary health care facilities in Brazil, namely, the University Hospital of Brasília (University of Brasília [UnB]) and the public regional hospitals of Asa Norte, Gama, Santa Maria, and Taguatinga (Brasília, Distrito Federal). Clinical procedures will be conducted according to a standard protocol approved by local institutional review boards under accession number CAAE 30846920.7.0000.0008, with participants included after voluntary signing of an informed consent form. The study protocol follows the recommendations of the STROBE (Strengthening the Reporting of Observational Studies in Epidemiology) statement for observational studies [16].

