### Statistical Analysis

Clinical and demographic data between groups of patients (severe vs nonsevere) as well as treatment profiles and differences in successive time points will be compared. To compare mean values of soluble biomarkers between groups, the *t* student test (or analysis of variance with post hoc test for multiple groups) or the nonparametric Mann-Whitney (or Kruskal-Wallis for multiple groups) test will be used as appropriate, according to the observed sample distribution features. The SAS 9.3 software (SAS Institute Inc) will be used with a significance level set at .05. The main binary outcomes will be analyzed by the estimation of relative risks using a log-binomial generalized model or by the area under the curve using trapezoidal methods. All personnel conducting laboratory procedures will be blinded regarding the patient status (severity of COVID-19). Receiver operating characteristic curves will determine cutoff points at which individual or combined scores of the molecular and cellular biomarkers become informative of the progression of COVID-19 cases, according to optimal sensitivity and specificity to identify the signature that best characterize each clinical status.

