## Results

This protocol is in the data collection phase. Study recruitment started in June 2020. At the end of July 2020, 30 T-branch and 85 D-branch patients were enrolled.

We expected to complete all patient inclusion by June 2020, but with the continuous increase in COVID-19 cases in Brazil, the authors decided to continue including patients until February 2021.

Data analysis is scheduled to start after all inclusion data have been collected.

The coagulation study branch, with thromboelastometry, has already been completed. Preliminary results confirm deregulation in initiation of the hemostasis process. The results are currently being analyzed and prepared for publication.

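### The sample size of 200 does not follow from its stated inputs (152, or 176 with continuity correction), and the 1:1 ratio behind it is neither secured by the design nor seen in the interim count

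*Protocol article*

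**What the plan says.** The Sample Size Calculation section of the protocol article rests on one comparison: "20% of patients who are critically ill have elevated TNF-α levels compared to 5% of patients who are noncritically ill". It sets the error rate with the words "Based on a bilateral 95% significance level" and ends: "a power of 80%, and a case-control ratio of 1, a sample size of 200 patients can be predicted". It names no test or formula and no allowance for losses or missing samples. The Statistical Analysis section gives a "significance level set at .05" and plans relative risks from a log-binomial model for the main binary outcomes.

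Study Design and Population describes a "multicenter, prospective cohort study of consecutive COVID-19 cases". Under Timeline, a patient's branch follows from severity and need for admission: T for mild/moderate, D for severe/critical. The article states no number to be enrolled in each branch. The Results section reports: "At the end of July 2020, 30 T-branch and 85 D-branch patients were enrolled". It adds that "the authors decided to continue including patients until February 2021", without returning to the ratio or the power.

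**The concern.** The paragraph prints both its inputs and its result, so a reader can check one against the other, and they do not match. A reader therefore cannot tell whether the study was sized for 80% power, for higher power, or for 80% after losses.

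The ratio is a second and separate matter. When severity decides the branch and cases are taken consecutively, the D:T split is an outcome of recruitment and not a design choice. An early count of 85 to 30 is 2.8 to 1, with the mild group, where the assumed event rate is only 5%, as the smaller one. If that continued, the information in the comparison would be limited by few patients and very few events on the mild side, and the power at 200 would not be that of a balanced design.

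**Working it through.** **Inputs.** From Sample Size Calculation: p1 = 0.20, p2 = 0.05, power 0.80, ratio 1, total 200. The level is two-sided 0.05, as Statistical Analysis confirms. From Results: 85 D-branch and 30 T-branch. Assumption: critically ill corresponds to the D-branch and noncritically ill to the T-branch.

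**1. Trying to reproduce 200.** The standard formula, with p̄ = 0.125, is

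n = [1.960·√(2·p̄(1−p̄)) + 0.842·√(p1(1−p1) + p2(1−p2))]² / (p1−p2)²

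= [1.960·√0.21875 + 0.842·√0.2075]² / 0.0225 = (0.9167 + 0.3834)² / 0.0225 = 75.1, so 76 per group and **152** in total.

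With continuity correction:

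n′ = (n/4)·[1 + √(1 + 4/(n·0.15))]² = (75.12/4)·(1 + 1.1640)² = 87.9, so 88 per group and **176** in total.

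Other two-sided versions at 80% power and 1:1 give these totals:

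| Method | Total |
|---|---|
| Arcsine | 140 |
| Unpooled variance | 146 |
| Pooled variance throughout | 154 |
| Exact Fisher | about 164 |
| Log odds ratio | 178 |
| Log relative risk | 188 |

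One-sided versions give 120, or 144 corrected. None gives 200.

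**2. What would give 200.** Each of these routes needs an input that the text does not state:
- 90% power, uncorrected: n = 100.06 per group, which rounds up to 202 in total.
- Continuity correction plus 12% losses: 176/0.88 = 200.

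**3. Power of 200 patients, by split and test.** If 85:30 held, 200·85/115 = 147.8 and 200·30/115 = 52.2, or about 148:52.

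| Test | 100:100 | 148:52 |
|---|---|---|
| Normal approximation | 90.0% | 77.6% |
| Exact chi-square | 92.1% | 80.5% |
| Fisher | 88.3% | 76.4% |
| Continuity-corrected, approximation | 85.6% | 68.0% |
| Continuity-corrected, exact | 87.2% | 69.7% |
| Log relative risk, Wald | 82.4% | 60.0% |

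The last row is closest to the planned log-binomial analysis. Its standard error is √(0.8/(0.2·nD) + 0.95/(0.05·nT)) = √(4/nD + 19/nT). At 100:100 this is 0.480, and log(4)/0.480 − 1.960 = 0.93, giving 82.4%. At 148:52 it is 0.626, and log(4)/0.626 − 1.960 = 0.25, giving 60.0%.

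**4. Sensitivity to the final split.** By normal approximation at 200 in total (D:T): 120:80 gives 88.1%, 130:70 gives 85.9%, 140:60 gives 82.2% and 145:55 gives 79.5%. If all 85 remaining patients were mild (85:115), power would be 89.9%. At a fixed 85:30 ratio, 80% power needs 210 (155 + 55) uncorrected or 244 (180 + 64) continuity-corrected.

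**5. Expected events.** Of 52 mild patients, 52·0.05 = 2.6 are expected to have elevated TNF-α. Of 100, it is 5.

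**The case against.** The best case for the plan has four parts.

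- **The discrepancy is on the safe side.** 200 exceeds every two-sided total above (the largest is 188), and power at 1:1 is above 80% on every test. An allowance of about 12% on 176 gives exactly 200, and a journal article may leave such an allowance to the full protocol. This stands as to consequence: at 1:1 the study is not too small. It does not repair the paragraph, which presents 200 as the result of the listed inputs.
- **85:30 is an interim count.** It was taken at 115 patients with recruitment open to February 2021, and the end of recruitment is set by date, so the total may pass 200. This stands. The lower power figures are conditional on the ratio lasting and on stopping at 200.
- **The sparse mild group comes mainly from the 5% assumption.** Only 5 events are expected even among 100 mild patients. This stands: imbalance worsens the sparsity but does not create it.
- **The 95% significance level is a slip of wording.** The .05 in Statistical Analysis settles it. This stands.

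Two stronger readings are tempting, and the article supports neither. A reader might infer that the stated 80% power fails whatever the split. In fact it is exceeded at 1:1, and at 148:52 the answer depends on the test, with exact chi-square still reaching 80.5%. A reader might also compute power at the 115 patients enrolled so far and report that very low figure. No such comparison is planned, because Results defers the analysis until inclusion data are complete.

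**Conclusion.** The stated inputs give 152 patients, or 176 with continuity correction, and not 200. That holds under every standard two-sided formula tried and needs no assumption beyond the printed inputs. Its effect is conservative at 1:1, where 200 patients give about 82% to 92% power depending on the test.

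The 1:1 premise is not secured by consecutive enrolment with branch set by severity, and it is at odds with the only count reported. If 85:30 lasted to 200, power would run from about 60% (log relative-risk Wald) to 80.5% (exact chi-square). On the simple normal approximation the shortfall is 2.4 points. These figures rest on the 20% and 5% rates, on equating critical illness with the D-branch, and on a final ratio that is not yet known. The two departures run in opposite directions and should be reported separately. The point is moderate: a figure that the study relies on needs restating, but the article does not show an under-sized study.

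**What to change.** Rewrite the Sample Size Calculation paragraph so that size and power agree:

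1. Name the formula. Then either state that 80% power needs 152 (176 with continuity correction) and that 200 gives about 90% at 1:1 by normal approximation, or state the loss allowance that leads to 200.
2. Report power for the expected D:T split, and later for the realised one, with the test named. Include the log relative-risk figure, since relative risks are the planned estimate.
3. Write 5% significance level in place of 95%.

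This costs wording only and leaves recruitment unchanged.

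Branch targets of 100 each are an option and not a requirement. From the July 2020 count they would need 15 more D-branch and 70 more T-branch patients, with the total still 200. The price is that D-branch enrolment would stop being consecutive once its target was reached, and restating the power avoids that.
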